## Abstract

Despite decades of research on the impact of interprofessional collaboration (IPC), we still lack definitive proof that team-based care can lead to a tangible effect on healthcare outcomes. Without return on investment (ROI) evidence, healthcare leaders cannot justifiably throw their weight behind IPC, and the institutional push for healthcare manpower reforms crucial for facilitating IPC will remain variable and fragmentary. The lack of proof for the ROI of IPC is likely due to a lack of a unifying conceptual framework and the over-reliance on the single-method study design. To address the gaps, this paper describes a protocol which uses as a framework the Quadruple Aim which examines the ROI of IPC using four dimensions: patient outcomes, patient experience, provider well-being, and cost of care. A multimethod approach is proposed whereby patient outcomes are measured using quantitative methods, and patient experience and provider well-being are assessed using qualitative methods. Healthcare costs will be calculated using the time-driven activity-based costing methodology. The study is set in a Singapore-based national and regional center that takes care of patients with neurological issues.

## 1. Introduction

Despite decades of research on the impact of interprofessional collaboration (IPC), we still lack definitive proof that team-based care can lead to tangible effect on healthcare outcomes [1,2]. In an age of evidence-based healthcare, the uncertainty around IPC’s return on investment (ROI) means that institutional support for IPC will remain variable and fragmentary; healthcare leaders and policymakers cannot justifiably throw their weight behind massive manpower reforms that are needed to facilitate IPC [3,4]. 

The lack of definitive proof for the ROI of IPC is likely due to two reasons: lack of a unifying conceptual framework with which to measure the healthcare outcomes of IPC, and over-reliance on the single-method study design for examining a phenomenon as complex and multi-faceted as IPC.

### 1.1. Conceptual Framework and Operationalization Issues

Notwithstanding IPC’s purported goal to improve patient care, IPC literature does not commonly report on its contribution to achieving the goals of healthcare, namely population health, patient experience, and cost of care, commonly known as Triple Aim [5]. In a systematic review [6] of interprofessional collaborative practices, only 25 or 18.8% of all the 133 studies reviewed reported one or two healthcare outcomes of the Triple Aim. Of these 25, 22 focused on patient experience of care alone and only 3 examined patient outcomes. None of the studies investigated the cost of IPC. The more recent Cochrane systematic review of randomized controlled trials of IPC interventions [2] shows that the situation has not changed. Out of the nine studies reviewed by Reeves and colleagues, only two measured IPC’s impact on healthcare outcomes, while the remaining seven examined more distal outcomes such as healthcare professionals’ (HCP) adherence to recommended practice, use of healthcare resources, team communication, and coordination. Whether and how these distal outcomes contributed to the healthcare system were unknown. Thus, to strengthen the evidence base for the ROI of IPC, it will be helpful to investigate IPC’s effectiveness using a unifying conceptual framework that encompasses all important components of healthcare outcomes.

A strong candidate is the Quadruple Aim [7], an expansion of the Triple Aim [5], where a fourth outcome—provider well-being—was added to the original framework. Although the Quadruple Aim framework was designed as a system of metrics for population health, the term population is not limited to people residing in a specific geographic area. The essence of this concept is its specificity and comprehensiveness, so that all the four outcomes can be measured in an integrated manner. In the context of IPC, population refers to patients with a specific disease receiving care from a specific IPC practice or practices in a specific healthcare institution and population health refers to patient outcomes. In short, the Quadruple Aim potentially can become a unifying framework with which researchers could identify outcomes for investigating IPC’s effectiveness holistically, and cumulatively this may help to strengthen the evidence base for IPC’s ROI.

### 1.2. Complex Problem Requiring Multimethod Approach

The other reason why IPC still lacks definitive proof of ROI could arguably be traced to the over-reliant use of a single-method (usually quantitative) study design [8]. While quantitative studies are useful, there are also limitations. Non-randomized quantitative studies have collectively produced a small body of evidence that consistently showed IPC to be effective in improving well-measured patient outcomes such as reducing fall risks [9], lowering blood pressure [10,11,12,13] and HbA1c in patients with diabetes [14,15]. However, when quantitative studies examined outcomes that involved social and behavioral dimensions, IPC was shown to have little or conflicting effects. A cluster RCT involving 236 hospital patients (intervention = 144 cases) found no significant differences in patients’ satisfaction with care and could not explain why [16]. Another large case control study involving more than 300 thousand primary care patients found that team-based primary care was associated with substantial reduction in emergency department and hospital utilization among chronically ill patients, but among healthier patients hospitalization and outpatient utilization actually increased [17]. The authors of this study speculated that coordinated care may have resulted in higher outpatient utilization among healthier patients but could not determine why hospitalization among this group also increased [17]. Such studies looking at one single aspect of the ROI of IPC are prone to generate mixed evidence which makes it difficult for healthcare leaders and policymakers to rely on them to inform their decisions on the investment of IPC.

Thus, the need for an approach that leverages both quantitative and qualitative methods in a complementary manner to evaluate IPC’s contribution to achieving the Quadruple Aim emerges. Quantitative methods are useful for measuring patient outcomes and cost of care as they are quantifiable. But for patient satisfaction and provider well-being, both of which involve interactions that are dynamic, variable, and non-linear [18], qualitative research is required for understanding how IPC works, for which patients and providers, in what context, and why [19].

We would like to propose an approach that may be new or unfamiliar to IPC researchers. Extant literature shows that the impact of IPC on the cost of care is often measured by shorter length of stay or lower rate of readmission [17,20,21]. However, such calculation methods have several limitations. The first study [17] stated that their primary source of data were administrative claims and not detailed clinical information retrieved from electronic health records, and there was erroneous attribution of patients to physicians, and physicians to practices. In the second study [20], the researchers were unable to use the calculation methods to determine which IPC process intervention had the greatest impact. In the last study of patients with chronic pancreatitis [21], the researchers omitted to track the cost associated with patients utilizing the services of an additional behavioral and psychiatric treatment team.

In view of the above limitations, this study presents time-driven activity-based costing (TDABC) [22] as an alternative research methodology. Originating from the field of management studies, TDABC has been recognized as the most accurate and efficient method of calculating the direct cost of complex team-based care to date [23]. Adopting the TDABC method to calculate the cost of IPC will thus be an important step towards accurately estimating the ROI of IPC.

### 1.3. Aims of Research Protocol

This study’s protocol aims to illustrate the feasibility of using the Quadruple Aim as a framework to measure IPC’s ROI by adopting a multimethod approach (Figure 1). The protocol describes two studies with several inter-related aims (see Supplementary Material: Figure S1. Proposal Workplan). Study 1 assesses IPC’s impact on patient outcomes and calculates the cost of care using quantitative methods. Study 2 seeks to understand the impact of team-based care resulting from IPC on patient experience and provider well-being using qualitative methods. Findings from these two inter-related studies are integrated to provide multi-faceted insights on IPC’s ROI, which may serve to guide organizations and policymakers on issues such as whether, how, and when healthcare budgets should be invested /disinvested in IPC.

## 2. Methods

This protocol paper describes two studies using the four dimensions of the Quadruple Aim framework to assess the impact of IPC on healthcare outcomes. The sections entitled ‘Study Setting’ and ‘Selection of the IPC Teams to Study’ will apply to both studies. However, the information for each study will be provided in a separate section to enhance readability.

### 2.1. Study Setting

The study setting is the National Neuroscience Institute (NNI) in Singapore, a national and regional center for treating the conditions of the brain, spine, nerves, and muscles. NNI operates out of two main hospitals (Tan Tock Seng Hospital and Singapore General Hospital) and four partner hospitals (Changi General Hospital, KK Women’s’ and Children’s Hospital, Khoo Teck Puat Hospital, and Seng Kang General Hospital) in Singapore. Specialist physicians, nurses, and allied health professionals (AHP) namely radiographers, therapists, psychologists, and medical technologists from the Departments of Neurology, Neurosurgery, Neuroradiology, Neurodiagnostic, and Neuromuscular Laboratories integrate their expertise and work together to care for patients in both inpatient and outpatient settings in these hospitals. Inpatient care is delivered by multidisciplinary teams of physicians, nurses, and AHP. These teams consist of a combination of core fixed members (physicians of varying seniority; four to six members) and fluid members (nurses and AHP of the wards). Outpatient care is mainly delivered by fixed teams of nurses and physicians (two to four members).

### 2.2. Selection of IPC Teams to Study

We will use a purposive sampling strategy known as positive deviance sampling, which allows researchers to compare individuals or communities who have discovered solutions to problems (positive deviants) with those peer individuals or communities who continue to struggle with the problem [24]. In this study, we define positive deviant as a group of HCP who manage to find solutions to work as an integrated team with common goals despite operating in an environment characterized by individualized episodic work practices.

Positive deviance sampling strategy is useful for facilitating culture change because it identifies examples that have found solutions to problems and difficulties within a given organization itself, rather than impose change from external sources [25,26]. Examples of positive deviance include three outpatient teams that care for patients with specific disease conditions: Persistent Concussion Clinic (PCC), Neuroimmunology Clinic (NC), and Epilepsy Clinic (EC) [27]. If the results of the proposed study show that the team-based approach produces better patient outcomes, provides care that patients need, and improves HCP well-being at a lower cost, then it could serve as a persuasive example for other services within the institution to adopt similar IPC practices.

### 2.3. Study 1 Design: Assessing IPC’s Impact on Patient Outcomes and Cost of Care

#### 2.3.1. Design

We will use a retrospective cohort study design for the assessment of patient outcomes and TDABC methodology for the assessment of cost of care.

#### 2.3.2. Study Sample

The population for population health in this study refers to patients with neurological disorders receiving care from the three selected team-based practices in NNI. For the assessment of patient outcomes, all patients who have been receiving care in the three selected team-based clinics since the start of these clinics (2021 for PCC, 2013 for NC, 2014 for EC) and have at least one-year follow-up period as of July 2022 will be included in the study sample.

The calculation of the cost of care does not involve sampling. We will survey all HCP involved in delivering care in the three selected clinics at the time of the study on the average amount of time they spend on each of the activities specified in a care pathway.

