#### 2.3.3. Measurements and Data Collection Plan

For patients receiving care in the PCC for head injuries which are acute, the primary patient outcome measure will be time to symptom resolution. The symptoms include vertigo, convergence insufficiency, cognitive functioning, psychological functioning, sleep disorders, and headache. For patients with epilepsy or neuroimmunological disorders which are chronic, the primary outcome measures include both disease activity and patient adherence to medication. Disease activity for epilepsy is measured by seizure frequency, and that for neuroimmunological disorders is measured by clinical (relapses) or radiological (MRI scan abnormalities) activity after initiation of immunotherapy. Medication adherence is based on patient self-reporting and is documented during each clinic visit. Secondary outcomes are process outcomes directly related to IPC for each clinic: rate of identification of symptoms by AHP for PCC, completion rate of screening for medication adherence, time to initiation of immunotherapy for NC, and tolerance and complications for EC. In addition to outcome measures, we will also collect data on patients’ demographic and clinical characteristics at the baseline (i.e., when they were first referred to these clinics), and treatment regimen during the study period. All data will be extracted from electronic medical records upon appropriate institutional approval.

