#### 2.3.4. Analysis Plan

Survival analysis will be used to characterize the primary outcome of time to symptom resolution for patients in PCC and the process outcome of time to initiation of immunotherapy for patients in NC. Cox proportional hazards regression analysis will be performed to examine these time-to-event outcomes after adjusting for the baseline demographic, clinical characteristics, and the treatment regimen during the follow-up period. Generalized Linear Mixed Models (GLMM) will be used to analyze the longitudinal primary outcomes of patients in NC and EC from the shortest period of one year to the longest period of eight years adjusting for baseline characteristics and treatment regimen during the follow-up period. Other process outcome results will be obtained through simple arithmetic calculations.

We will calculate the cost of each activity along the care pathway by multiplying the time spent on each activity by a specific HCP and the unit cost for the HCP performing the activity. The cost of an episode of care will be the sum of the costs of all activities on the care pathway. The concept of ‘episode of care’ in this protocol will be determined by the care pathway of the respective clinics. The total cost for each clinic will be calculated by multiplying the cost of each episode of care by the volume of patients treated during the study period.

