### 2.4. Study 2 Design: Understanding How IPC Impacts Patient Experience and Provider Well-Being

#### 2.4.1. Sampling and Recruitment

For the patient experience component of Study 2, all patients who have been receiving care in the three selected team-based clinics since the start of these clinics (2021 for PCC, 2013 for NC, 2014 for EC) and have at least a one-year follow-up period as of July 2022 will meet the inclusion criterion. We will be using a purposive sampling strategy known as team sampling unit (TSU), where we interview [29] the patients as well as the HCP they identify as being vital to their care. The interviews will be conducted separately. This sampling strategy has been successfully used to produce rich analyses by researchers studying team-based care for patients with severe chronic obstructive pulmonary disease [30,31] and advanced heart failure [32,33]. As TSU has the potential of offering more opportunities for data triangulation than individual interviews, it seems particularly relevant for our study as it will enable us to collect multiperspective information to derive a more complete understanding of whether and how PCC, NC, and EC provide team-based care that meets patients’ needs. TSU is recommended to consist of the patient and at least two HCPs [31]. Thus, we will also plan our recruitment strategy in a similar fashion. 

We will also seek the patients’ consent to shadow them [34,35]. We will explain that shadowing will allow us to better understand how they actually experience care in the PCC, NC, and EC settings. However, should patients only consent to be interviewed and not be shadowed or identify the HCP, we will still include them in the study as it is often challenging to recruit patients. For patients who agree to identify the HCP, the latter will be subsequently voluntarily recruited. Both patients and HCP will be interviewed at a time and location of their choosing.

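### The one-year follow-up entry rule does not say whether it means time since referral or time kept in care; the second selects on the PCC primary outcome, the first needlessly drops recent PCC referrals

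*Protocol article*

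**What the plan says.** Section 2.3.2 (Study Sample) takes "all patients who have been receiving care in the three selected team-based clinics since the start of these clinics", gives the opening years as "2021 for PCC, 2013 for NC, 2014 for EC", and adds the condition that patients "have at least one-year follow-up period as of July 2022 will be included in the study sample". One sentence covers all three clinics.

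Section 2.3.3 places baseline at the time "when they were first referred to these clinics". It sets the PCC outcome as follows: "For patients receiving care in the PCC for head injuries which are acute", "the primary patient outcome measure will be time to symptom resolution". Data come from electronic medical records.

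Section 2.3.4 analyses the PCC outcome by survival methods and Cox regression, with no minimum period stated. It analyses the longitudinal NC and EC outcomes by generalized linear mixed models (GLMM) "from the shortest period of one year to the longest period of eight years".

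Section 2.4.1 repeats the rule for the patient interviews: patients who "have at least a one-year follow-up period as of July 2022 will meet the inclusion criterion".

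The Conclusions describe Study 1 as single-arm, to be interpreted by an informal comparison with published results. Their list of limitations does not mention the entry rule.

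**The concern.** The clock starts at first referral, but entry depends on something that accrues afterwards. In a clinic for acute injury, recovery is a natural reason for follow-up to end. If the required year is time in care, an early recovery removes the patient from the sample while slow resolvers stay in, so the sample is selected on the primary outcome itself. In NC and EC, patients who disengage, move away or die in the first year would also be missing, and disease activity and adherence would be estimated in stayers only.

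Study 1 has no internal comparator to absorb such a distortion. Its result is set beside published outcomes, so a shift in the PCC median, or in NC and EC adherence, goes straight into the interpretation.

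**Working it through.** The plan states no sample size, event count or expected resolution time, so there is no figure of its own to reproduce. The check compares two readings of the rule.

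**Inputs from the article:** entry needs one year as of July 2022; PCC opened in 2021 (month not given); baseline is first referral; the PCC outcome is time to symptom resolution.

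**Assumed inputs, none from the article:** exponential time to resolution with true median *m*; exponential stay in clinic after resolution with mean 1, 3 or 6 months; PCC opening in January 2021 with even referrals.

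**Reading A: at least 12 months since referral, discharged patients kept.** Entry depends on calendar date only. In a simulation of 400,000 patients per scenario, the Kaplan-Meier median equals the true one throughout: 2.0, 3.0, 6.0, 9.0 and 12.0 months.

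**Reading B: at least 12 months actually in care.** With a = ln 2 / *m* and b = 1 / mean stay, the share kept is

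(b·e^(−12a) − a·e^(−12b)) / (b − a).

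For *m* = 3 and a mean stay of 1 month, a = 0.231 and b = 1, and the share is 0.0625 / 0.769 = 0.081. The simulation also gives 0.081.

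| True median (months) | Share kept, stay 1 / 3 / 6 | Observed median (months), stay 1 / 3 / 6 |
|---|---|---|
| 2 | 2% / 9% / 25% | 12.8 / 7.2 / 3.6 |
| 3 | 8% / 16% / 32% | 13.8 / 10.6 / 6.3 |
| 6 | 28% / 37% / 51% | 16.9 / 14.5 / 11.8 |
| 9 | 43% / 51% / 62% | not reached / 17.8 / 15.2 |
| 12 | 53% / 60% / 69% | not reached / not reached / 18.4 |

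The shift is towards slower resolution in every cell. For a true median of 6 months, resolution by month 6 falls from 50% to between 0% and 22%.

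**A cruder version of Reading B.** Let d be the share of patients resolved by month 12 who are discharged before one year. With *m* = 3, F(12) = 1 − 2^(−4) = 0.9375.
- d = 0.80: included = 0.0625 + 0.20 × 0.9375 = 0.25. Resolved at 12 months = 0.1875 / 0.25 = 75%, against a true 94%. The median solves F(t) = 0.625, so t = 4.2 months.
- d = 0.95: included = 0.0625 + 0.0469 = 0.1094. Resolved at 12 months = 0.0469 / 0.1094 = 43%, so the median exceeds 12 months.
- d = 1: nobody in the sample resolves in the first year.

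**NC and EC under Reading B.** If 15% leave in the first year with 50% adherence, against 85% in stayers, the whole group has 0.85 × 0.85 + 0.15 × 0.50 = 0.7975, about 80%. The sample would show 85%.

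**PCC referrals lost under Reading A.** Opening in January 2021 gives 19 calendar months to July 2022, of which January to July 2021 (7) qualify, so 12/19 = 63% are lost. Opening in April gives 12/16 = 75% lost, and opening in July gives 12/13 = 92%. A later opening would leave nobody eligible.

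**The case against.** A reader might infer that the protocol excludes recovered PCC patients, and that the one-year minimum in Section 2.3.4 proves it. The documents do not support that. The minimum stands in the sentence on NC and EC; PCC is handled separately by survival methods. Even for NC and EC it is inconclusive. Elapsed time since referral would also give a one-year minimum, and the eight-year maximum is about the calendar time from the 2014 EC opening, although NC's 2013 opening would allow about nine. Section 2.3.2 speaks of all patients, fixes the year at a calendar date and excludes no discharged patient by name. Records of discharged patients can still be extracted.

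The other side's further points also have weight. Every size above rests on assumed inputs. The clinic is for persistent concussion, so recovery may not be fast. Under the adverse reading PCC looks worse rather than better, so no false favourable result would arise there. The study is presented as a feasibility exercise, and a condensed article may leave an operational definition to a fuller document.

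These points make the bias conditional; they do not remove the problem. The wording about patients who have been receiving care, and Section 2.3.4's use of the follow-up period as the time over which treatment is recorded, keep the time-in-care reading plausible. Nothing says that discharged patients stay in. Slower recovery does not rescue the estimate, since a true median of 6 months still appears as 11.8 to 16.9. The elapsed-time reading has its own cost, which clarification alone would not remove.

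**Conclusion.** The point holds in conditional form. The entry rule is ambiguous, and neither reading serves the PCC primary outcome well. If the year is time in care, time to symptom resolution is selected on the outcome and biased towards slow recovery, NC and EC results describe one-year stayers, and the comparison with published outcomes is distorted. If it is time since referral, there is no selection on the outcome. The cost is then precision: PCC loses all referrals after about July 2021, although censoring in the planned survival analysis would accommodate them.

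The direction of the PCC bias under the time-in-care reading follows from the mechanism. Its size depends on recovery and discharge times, and the referral loss on the opening month and referral flow. The article gives none of these, so the figures illustrate what could happen and do not measure it.

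The repetition of the rule in Section 2.4.1 is a lesser matter. That sampling is purposive and makes no population estimate, but under the time-in-care reading it would leave out the experience of patients who recovered or left early.

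**What to change.** - **Section 2.3.2:** define Study 1 eligibility as first referral from clinic opening to the data cut-off, with no minimum follow-up. State that discharged patients and those who stopped attending are kept.
- **Section 2.3.4:** start the PCC clock at first referral and censor unresolved patients at last contact or cut-off. Let NC and EC patients contribute whatever follow-up they have to the GLMM, and amend the stated one-year minimum. Censoring at last contact assumes that those who stop attending resemble those who remain, and the plan should say so.
- **Sensitivity analysis:** if a cohort with a full potential year is wanted, define it by referral on or before July 2021, whatever the later attendance.
- **Section 2.4.1:** state that discharged patients are also eligible for interview.

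The cost is a sentence or two in each section, some extra chart extraction, and shorter average follow-up. Eligibility should be settled before extraction begins.
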